### Initial Therapy Procedure

After a thorough examination and diagnosis, full-mouth ultrasonic scaling will be performed as part of the initial therapy. The patients will be given additional plaque control instructions until their plaque scores drop below 25%. Prior to surgery, a diagnostic cast will be constructed for each patient in order to assess the maxillomandibular relationship. Every patient’s preoperative and postoperative clinical photographs will be taken. All patients’ oral hygiene and gingival status will be reviewed on the day of surgery, three, and nine months apart.

### Clinical Measurements

#### Indices

All patients’ oral hygiene and gingival status will be reviewed on the day of surgery, 3, and 9 months apart.

#### Plaque Index

The plaque index (PI) will be calculated by Turesky-Gilmore-Glickman Modification of Quigley-Hein 1970 [19]. The presence of plaque will be evaluated on the labial, buccal, and lingual surfaces of all teeth after the application of the disclosing agent (Table 1).

**Table 1 table1:** Scoring system for the Turesky-Gilmore-Glickman modification of the Quigley-Hein plaque index.

Score	Criteria
0	Absence of plaque.
1	Distinct plaque deposits on the cervical surface of a tooth.
2	Thin, uninterrupted layer of plaque (up to 1 mm) covering the tooth's cervical margin.
3	Plaque band broader than 1 mm but covering less than one third of the crown.
4	Plaque covering not less than one third but less than two thirds of the crown.
5	Plaque that covers two thirds or more of the crown.

The PI value for the tooth will be calculated by splitting all the points around it by two. The PI score for an individual person will be gained by summing the PI scores of all teeth and dividing by the quantity of teeth inspected.

#### Papillary Bleeding Index

A periodontal probe (William Calibrated Probe) will be precisely introduced mesially into the gingival sulcus at the apex of the papilla and will then be advanced coronally to the tip of the papilla. On the same papilla, this was repeated on the distal side. On a scale of 0-4, the degree of potential bleeding was evaluated according to the method described by Checchi et al [20,21].

The papillary bleeding index score per individual will be calculated by adding up all papillary bleeding index scores to the number of surfaces analyzed.

### Radiographic Measurements

Prior to implant insertion, immediately following implantation (0 months) and 3 and 9 months post surgery, bone density (using CBCT) will be measured. Implant stability will be evaluated both immediately following installation (0 months) and 3 and 9 months post surgery. ISQ will be measured using the Osstell device (Osstell AB).

In order to establish the density of the surgical site, a preoperative radiographic evaluation will be performed using CBCT, and the bone density in HU in the coronal (mesial and distal aspect) and apical region of extraction socket, and crestal bone levels will be assessed. The measuring tool in the software will analyze the crestal bone levels at the crest of the bone (first and second threads) and at the apical thirds (last two threads). The bone density will be measured using Planmeca Romexis (Planmeca Oy) software.

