## Methods

### Overview

This single-arm study will aim at assessing the efficiency of the osseodensification system in enhancing the bone density and volume in cases with delayed implant placement. It will assess the osseodensification impact on the healing of bones and osseointegration, which is by comparing the clinical and radiographic outcomes before surgery and after it.

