### Surgical Procedure

All patients will be given prophylactic antibiotic 1 hour before surgery (amoxicillin 500 mg). Depending on the site of implant placement, a nerve block or infiltration anesthesia will be used to numb the area using a local anesthetic solution of 2% lignocaine solution with 1:100,000 adrenaline.

The dental implant procedure will begin with the mid-crestal incision in the gingiva at the implant site, followed by the gentle reflection of the full-thickness mucoperiosteal flap to expose the underlying bone. Sequential osseodensification drills of increasing diameter will then be used to prepare the bone for implant placement, creating the osteotomy to ensure the site is appropriately sized and shaped for the implant. Osseodensification used during this stage will ensure condensation of native bone and enhance the bone density, facilitating the conditions for improvement in implant stability. After site preparation, a titanium dental implant will be carefully placed into the osteotomy site, ensuring optimal primary stability, which will be crucial for successful osseointegration. The flap will be repositioned and sutured by 3-0 silk suture material, with placement of a healing abutment or cover screw to protect the implant during the healing process.

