### Statistical Analysis

The mean (SD) values will be used to represent all quantitative data. A repeated measures design is preferable to independent or paired 1-tailed *t* tests, which assume just two dependent observations, because measurements will be made for the same participants at three different time points (baseline, three months, and nine months). In order to assess the mean changes in ISQ values and bone density (HU) throughout the three time points, statistical analysis will be carried out using repeated measures ANOVA. Greenhouse-Geisser corrections will be used if the sphericity assumption is violated. To find significant differences between particular time points (eg, baseline vs 3 months, baseline vs 9 months, and 3 months vs 9 months), post hoc pairwise comparisons with Bonferroni adjustment will be performed. The significance level will be set at *P*<.05.

Descriptive statistics (frequency and percentage) will be presented for categorical variables (eg, implant survival and presence or absence of peri-implant disease).

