### Expected Outcomes

It is hypothesized that osseodensification may enhance mechanical retention and primary implant stability by increasing peri-implant bone density and bone-to-implant contact. Within the scope of this pilot study, osseodensification is expected to demonstrate potential improvements in bone compaction and implant stability when compared to baseline values in D2-D3 bone sites.

Based on previous preclinical and limited clinical evidence, it is anticipated that osseodensification could contribute to improved early osseointegration and reduced micromotion. However, these outcomes remain to be verified, as this exploratory protocol is designed primarily to assess feasibility, short-term trends, and methodological reliability, rather than to establish definitive clinical efficacy.

The findings from this pilot study will therefore serve as preliminary data for refining hypotheses, estimating effect sizes, and informing the design of future RCTs comparing osseodensification with conventional osteotomy techniques.

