
Nonetheless, it is necessary to recognize some limitations. Since improvements will only be evaluated in relation to baseline values, the single-arm design without a comparator group (conventional osteotomy) limits the capacity to draw concrete conclusions about the superiority of osseodensification. The 9-month follow-up period might not accurately represent long-term implant survival and performance, even though it is long enough to record short- to midterm outcomes of implant stability and bone density. Given the technical sensitivity of osseodensification, operator-related procedure variability may also affect results, even with calibration efforts. In addition, while the inclusion criteria, which concentrate on individuals with intact alveolar walls, adequate oral hygiene, and D2-D3 bone quality, lessen confounding, they may also introduce selection bias and restrict external validity to more diverse real-world populations.

In both high- and low-density bone sites, the findings of this exploratory study will be used as pilot data to guide the design of RCTs that compare osseodensification with traditional drilling. The impact of baseline patient characteristics, including bone quality, systemic diseases, oral hygiene level, or site location on the efficacy of osseodensification should also be investigated in larger research. Furthermore, to demonstrate the external validity and practicality of this method, practical clinical trials with bigger and more varied patient groups would be required.

Presentations at national and international dental research conferences and the submission of full-length publications to peer-reviewed journals will be used to share the trial’s findings. To help with knowledge translation and incorporation into clinical practice, the results will also be shared with the institution’s participating patients and doctors.

It is anticipated that the trial will demonstrate, within the constraints of this single-arm exploratory protocol, how osseodensification may improve bone density and implant durability in delayed implant implantation at locations with D2 and D3 bone quality. The expected results will assist in establishing feasibility, produce effect size estimates, and guide the design of future RCTs that can more definitively evaluate the role of osseodensification in implant dentistry, even though definitive conclusions cannot yet be formed.

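### All three ISQ readings follow the osseodensified osteotomy, so improvement in implant stability against baseline cannot be attributed to osseodensification

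*Protocol article*

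**What the plan says.** **Order of events.** Under Surgical Procedure the intervention comes first: "Sequential osseodensification drills of increasing diameter will then be used to prepare the bone for implant placement". The implant follows: "After site preparation, a titanium dental implant will be carefully placed into the osteotomy site".

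**ISQ timing.** Under Radiographic Measurements: "Implant stability will be evaluated both immediately following installation (0 months) and 3 and 9 months post surgery". The same section treats bone density differently: "Prior to implant insertion, immediately following implantation (0 months) and 3 and 9 months post surgery, bone density (using CBCT) will be measured".

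**Test.** Statistical Analysis applies repeated measures ANOVA "In order to assess the mean changes in ISQ values and bone density (HU) throughout the three time points", followed by the three Bonferroni-adjusted pairwise comparisons among baseline, 3 and 9 months.

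**Use of the result.** Expected Outcomes hypothesises a gain in primary stability and then states that "osseodensification is expected to demonstrate potential improvements in bone compaction and implant stability when compared to baseline values in D2-D3 bone sites". Sample Size Calculation makes ISQ the outcome on which the 22 patients rest. The Introduction and Expected Outcomes both say that the findings will supply effect sizes for later randomised trials.

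**Stated limitation.** The Discussion (Principal Findings) says that "improvements will only be evaluated in relation to baseline values" and that, without a conventional-osteotomy arm, superiority cannot be firmly concluded.

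**The concern.** A baseline supports a before-and-after statement only if it precedes the intervention. For ISQ it does not. The reading called baseline is taken with the implant already seated in the osseodensified bone, which is the moment at which primary stability, the hypothesised target, is expressed.

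Two things are at stake. A significant rise from 0 to 3 or 9 months would be reported, under the wording of Expected Outcomes, as improved stability from osseodensification, although the contrast does not isolate that. And the mean ISQ change could be passed to a future randomised trial as a treatment effect, when part or all of it may be the course of any healing implant.

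**Working it through.** **1. The plan's own figure.** The stated sample size is 22. The ANOVA inputs in Sample Size Calculation are f = 0.40, alpha 0.05, power 0.90, correlation 0.5 and three times. The noncentrality is λ = f² × n × 3 / (1 − 0.5).
- n = 15: λ = 0.16 × 15 × 3 / 0.5 = 14.4, power 0.906. This is the smallest n that reaches 0.90.
- n = 22: λ = 21.12, power 0.984.

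The paired inputs (difference 4, SD 1.86, z values 1.96 and 2.57) give ((1.96 + 2.57) × 1.86 / 4)² = 4.4, so 5 patients, or 9 with a factor of 2. The figure of 22 is therefore not reproduced. That is a separate matter and does not affect this point; n = 22 is used below because it is the planned size.

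**2. What the tested contrasts contain.** Write a patient's ISQ at time t as

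ISQ(t) = P + D + h(t) + s(t), with h(0) = s(0) = 0,

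where P is the stability that conventional preparation would have given at placement, D the effect of osseodensification on primary stability, h(t) ordinary healing, and s(t) any further effect of osseodensification on secondary stability.

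| Contrast | Content |
|---|---|
| 3 months − 0 months | h(3) + s(3) |
| 9 months − 0 months | h(9) + s(9) |
| 9 months − 3 months | h(9) − h(3) + s(9) − s(3) |

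D appears in none of them. The ANOVA tests whether these contrasts are all zero, so D is absent there too. What remains is h plus s, and one arm gives only their sum.

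**3. Contrast with bone density.** Density has a reading before insertion, so a change from that reading does span the intervention. The argument in step 2 does not carry over to it.

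**4. Illustration of size.** Assume that osseodensification does nothing (D = 0, s = 0) and that healing alone adds h ISQ units. The documents give no healing-alone figure, so h = 1 and h = 2 are assumptions. The SD range 1.5 to 2.5 is from Sample Size Calculation, read here as the SD of the change. The test is a two-sided paired t test with 21 df and noncentrality h × √22 / SD. The critical value is 2.080 at 0.05 and 2.601 at 0.05/3.

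| h (assumed) | SD | Noncentrality | P(significant), 0.05 | P(significant), Bonferroni |
|---|---|---|---|---|
| 1 | 1.5 | 3.13 | 0.85 | 0.70 |
| 1 | 2.5 | 1.88 | 0.43 | 0.26 |
| 2 | 1.5 | 6.25 | >0.99 | >0.99 |
| 2 | 2.5 | 3.75 | 0.95 | 0.86 |

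A significant ISQ rise is thus quite possible, and at 2 units likely, with no osseodensification effect at all.

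**The case against.** The strongest reply is that the article already discloses the problem. It is a single-arm pilot, Expected Outcomes puts feasibility and short-term trends ahead of definitive efficacy, and the Discussion concedes that superiority cannot be concluded without a comparator. ISQ describes the interface between implant and bone, so no reading can exist before an implant does, and no measurement is wrong or missing. The aims also include osseointegration, and the article cites secondary stability, to which the 0-3-9 month course is relevant.

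Much of this stands. What the limitation leaves out is narrower: it judges improvement against baseline without saying that the ISQ baseline already contains the intervention. The pilot label does not cover this either, since Rationale for the Study's Design names efficacy in the main goal and calls the within-subject design appropriate.

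Several stronger readings are tempting, but the documents do not support them:
- *The ISQ change measures healing and nothing else.* An effect on secondary stability could be part of it. The accurate statement is that the two cannot be separated.
- *A significant result is near certain from healing alone.* The 3 to 5 unit gains in Sample Size Calculation come from studies of osseodensification, so power at 4 units says nothing about healing alone. At an assumed 1 unit the probability is well short of certainty.
- *The Overview claims a before-and-after ISQ comparison.* It speaks of "comparing the clinical and radiographic outcomes before surgery and after it" with regard to bone healing and osseointegration, and does not name ISQ.
- *The Discussion calls the baseline untreated.* It does not.
- *An external conventional-drilling benchmark would repair the analysis.* The documents give no such ISQ value. The Introduction itself says that earlier studies differ in measurement protocols, timing and implant systems, so a benchmark would be confounded.

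**Conclusion.** The point holds for ISQ. Every ISQ contrast lies wholly after the intervention, so the hypothesised effect on primary stability cannot appear in any of them, and an improvement in stability against baseline cannot be attributed to osseodensification. This rests on the order of events stated under Surgical Procedure and Radiographic Measurements, which no other section contradicts; it does not depend on a numerical assumption.

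The probabilities illustrate consequence only. They rest on assumed healing gains, on reading the quoted SD range as the SD of change, and on complete data for 22 patients. The fault lies in what the ISQ test is said to show. The readings themselves are sound, and the point does not extend to bone density.

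**What to change.** 1. In Statistical Analysis and the outcome section, report 0-month ISQ as the primary-stability result, as a mean with 95% CI. With 22 patients the half-width is 2.080 × SD / √22 = 0.44 × SD, where SD is the between-patient SD at placement (not given in the article). State that this describes a level and is not an effect estimate.
2. Describe the 0-3-9 month ISQ analysis as stability development after placement, and state that it is not evidence of an osseodensification effect.
3. In Expected Outcomes, take implant stability out of the sentence on improvement against baseline values.
4. In the limitations paragraph of the Discussion, add that the ISQ baseline is taken after the intervention.
5. State that the ISQ change will not be used as a treatment effect size when a randomised trial is planned.

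**Cost.** Wording and labelling only: the same visits, readings and patients. The article reports that no outcome data are available yet, so the change can be made before results are seen. The downside is that the ISQ P value no longer supports an efficacy statement, and that question is left to a controlled trial.

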### Surgical Procedure

All patients will be given prophylactic antibiotic 1 hour before surgery (amoxicillin 500 mg). Depending on the site of implant placement, a nerve block or infiltration anesthesia will be used to numb the area using a local anesthetic solution of 2% lignocaine solution with 1:100,000 adrenaline.

The dental implant procedure will begin with the mid-crestal incision in the gingiva at the implant site, followed by the gentle reflection of the full-thickness mucoperiosteal flap to expose the underlying bone. Sequential osseodensification drills of increasing diameter will then be used to prepare the bone for implant placement, creating the osteotomy to ensure the site is appropriately sized and shaped for the implant. Osseodensification used during this stage will ensure condensation of native bone and enhance the bone density, facilitating the conditions for improvement in implant stability. After site preparation, a titanium dental implant will be carefully placed into the osteotomy site, ensuring optimal primary stability, which will be crucial for successful osseointegration. The flap will be repositioned and sutured by 3-0 silk suture material, with placement of a healing abutment or cover screw to protect the implant during the healing process.

### Postoperative Care

Patients will be asked to rinse mouth with 0.2 % chlorhexidine (afterwards, twice daily for 2 wk). All patients will be instructed to apply cold fomentation starting immediately and for the next 24 hours. Amoxicillin+clavulanate (625 mg), together with a systemic analgesic aceclofenac+paracetamol+serratiopeptidase (440 mg), will be administered for 5 days. After 7 days, suture removal will be performed.

### Clinical Examination

Implant mobility will be evaluated with the help of the Osstell device instrument (Osstell AB), which is a resonance frequency analysis (RFA) tool. Larger ISQ values will indicate that the implant-bone interface is more stable [22,23].

### Radiographic Measurement

Preoperatively, 3 months, and 9 months post surgery, bone density at the implant site will be evaluated using CBCT. The coronal (mesial and distal) apical portions of the implant site will be assessed for bone density, which will be expressed in HU. To evaluate early changes in bone remodeling, the mean bone density values at baseline and 3 months will be compared. In order to identify additional changes over time and gain insight into the osseointegration and bone healing process, the mean bone density values at 3 and 9 months will also be examined.

### Statistical Analysis

The mean (SD) values will be used to represent all quantitative data. A repeated measures design is preferable to independent or paired 1-tailed *t* tests, which assume just two dependent observations, because measurements will be made for the same participants at three different time points (baseline, three months, and nine months). In order to assess the mean changes in ISQ values and bone density (HU) throughout the three time points, statistical analysis will be carried out using repeated measures ANOVA. Greenhouse-Geisser corrections will be used if the sphericity assumption is violated. To find significant differences between particular time points (eg, baseline vs 3 months, baseline vs 9 months, and 3 months vs 9 months), post hoc pairwise comparisons with Bonferroni adjustment will be performed. The significance level will be set at *P*<.05.

Descriptive statistics (frequency and percentage) will be presented for categorical variables (eg, implant survival and presence or absence of peri-implant disease).

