### Sample Size Calculation

Based on the key outcome variable, implant stability (ISQ values), which will be evaluated at baseline, 3 months, and 9 months post surgery in the same patients, the sample size for this study was estimated. The repeated measures ANOVA framework was chosen because it takes into consideration correlations between several observations made on the same subject.

According to earlier research assessing osseodensification, the average ISQ improvements were between 3 and 5 units, with SDs varying between 1.5 and 2.5. For repeated measures over three time points, a modest effect size (f=0.40) was anticipated using these estimations. The necessary sample size was determined to be 22 patients with α=.05, power=0.90, and correlation among repeated measurements set at 0.5 (G*Power 3.1; Heinrich Heine University Düsseldorf; repeated measures ANOVA, within-subject variables).[18]

This sample size will guarantee feasibility in the framework of an exploratory clinical protocol and offer enough power to identify clinically significant variations in bone density and implant stability over the course of the trial.

The calculation used the formula stated below, where the input parameters are as follows:

The input parameters are α (for a 95% CI)=1.96, : 0.01 (power=1β=99%)=2.57, and mean difference 4 (SD 1.86).

The minimum paired sample size needed is 22 participants.

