### Primary and Secondary Outcome Variables

This study’s primary outcome variables will involve evaluating bone density and volume changes in delayed implant placement locations using radiographic techniques including CBCT to ascertain how the osseodensification system affects compaction and bone preservation. RFA will be used to determine the ISQ, which is another important component. Additionally, the study will use radiographic techniques to analyze BIC over time in order to evaluate osseointegration success.

The clinical and radiographic evaluation of bone healing, as determined by peri-implant bone level changes using CBCT, will be the main emphasis of the secondary outcome variables. Functional loading results, the absence of implant mobility, and the absence of peri-implant radiolucency will also be used to assess the implant success rate. In order to examine the long-term efficacy and safety of implants placed using the osseodensification system, the study will also monitor complication rates, such as early or late implant failure, marginal bone loss, and the incidence of peri-implantitis.

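### The repeated measures ANOVA named for ISQ and HU discards a patient's observed values when one of three visits is missing; a mixed model would keep them, and implant failure needs its own statement

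*Protocol article*

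**What the plan says.** All references are to the protocol article.

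- **Method.** Under Statistical Analysis, for both ISQ and HU, "statistical analysis will be carried out using repeated measures ANOVA". Measurements are taken "at three different time points (baseline, three months, and nine months"), and "Greenhouse-Geisser corrections will be used if the sphericity assumption is violated". To locate differences between visits, "post hoc pairwise comparisons with Bonferroni adjustment will be performed".
- **Expected gaps.** Ethical Considerations lets participants withdraw at any time. Primary and Secondary Outcome Variables lists "complication rates, such as early or late implant failure, marginal bone loss, and the incidence of peri-implantitis" among the secondary outcomes.
- **Failures.** Statistical Analysis reports implant survival as a frequency and percentage, and does not connect it with the ISQ and HU analysis.
- **Sample size.** Sample Size Calculation states that "The minimum paired sample size needed is 22 participants".

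**The concern.** Univariate repeated measures ANOVA with a sphericity correction works on a complete patient-by-visit table. A patient seen at baseline and 3 months but not at 9 months contributes nothing, although two of the three values are in hand. The article names this method while anticipating the two events that create gaps.

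The two events differ in kind:

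- **A missed visit or withdrawal** leaves a value that exists but was not recorded.
- **A failed implant** has no later ISQ at all, and an HU reading at the site is no longer a peri-implant value. A mean change computed without it describes surviving implants only.

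The article wants its results to supply effect sizes for later randomised trials. An estimate restricted to surviving, fully attending patients, and not labelled as such, would carry that restriction into those designs.

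**Working it through.** **1. Does the named method need complete records?** Yes. A standard routine for repeated measures ANOVA, given 22 patients and three visits with one cell removed, stopped and reported unbalanced data. The patient must be dropped or a value imputed. The article mentions neither imputation nor a mixed model.

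**2. How much is discarded?** The article gives no loss rate, so this is an illustration. Let a proportion p miss each follow-up visit independently, with baseline always observed.

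- Complete cases = 22(1−p)²
- Values observed = 22 + 2 × 22(1−p)
- Values used = 3 × 22(1−p)²

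| p (assumed) | Complete cases | Values observed | Values used | Discarded |
|---|---|---|---|---|
| 5% | 19.9 | 63.8 | 59.6 | 4.2 (7%) |
| 10% | 17.8 | 61.6 | 53.5 | 8.1 (13%) |
| 15% | 15.9 | 59.4 | 47.7 | 11.7 (20%) |

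**3. How large could the bias be?** The inputs from Sample Size Calculation are a mean change of 4 and SD 1.86, the latter taken as the SD of change. Suppose the k lowest of 22 on some variable X are lost, and let r be the correlation of X with the change. For normal data:

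shift = r × 1.86 × φ(z)/(1−p), with p = k/22 and z the p-quantile of the standard normal.

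For k = 2: p = 0.091, z = −1.335, φ(z) = 0.164 and φ(z)/(1−p) = 0.180.

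First, take SD 1.86 at each visit and correlation 0.5 between visits (the article's figure for repeated measurements). The SD of change is then again 1.86.

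- X = 9-month ISQ, r = +0.5: shift = 0.5 × 1.86 × 0.180 = +0.17, giving 4.17 (4% too high).
- X = baseline ISQ, r = −0.5: shift = −0.17, giving 3.83 (4% too low).
- X = 3-month ISQ, r = 0: shift = 0, giving 4.00.

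With one or three patients lost, the same formula gives 4.09 or 4.24 for loss on 9-month ISQ. Simulation gives 3.91 or 3.77 for loss on baseline.

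The article gives no baseline SD, so the first case was repeated with 9-month ISQ = baseline + independent change, where r = 1.86/√(SD_b² + 1.86²).

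- Assumed baseline SD 5: r = 0.349, shift = 0.349 × 1.86 × 0.180 = 0.12 (2.9%).
- Assumed baseline SD 1.86: r = 0.707, shift = 0.707 × 1.86 × 0.180 = 0.24 (5.9%).

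Losing the two least stable implants therefore overstates the change by roughly 3 to 6%.

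**4. What does a mixed model recover?** Take the baseline case in step 3, with the two lowest-baseline patients lost after baseline. This loss depends only on an observed value, so it is missing at random. Likelihood estimation uses their baseline values and recovers the true change of 4 on average, where complete-case ANOVA gives about 3.83. If loss depends on the unobserved 9-month value itself, the model does not remove the bias.

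**The case against.** The strongest objection is scope. The article never says that only complete cases will be analysed, and a full protocol or analysis plan that is not shown could add imputation. Failures are not hidden either, because survival and failure are reported. The study is an exploratory pilot that disclaims firm conclusions. It also selects low-risk patients, so failures may be few.

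This limits the weight of the point but does not remove it. The point rests on the method the article names, not on the absence of a missing-data section. A method that tolerates gaps is available at almost no cost.

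A second objection also stands: a mixed model does not cure implant failure. Under missing at random it would extrapolate stability for an implant that is no longer there. Failure must be dealt with separately.

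A reader might infer four stronger points that the documents do not support.

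- **Lost power.** Under the stated inputs ("a modest effect size (f=0.40) was anticipated using these estimations", α 0.05, correlation 0.5, sphericity), repeated measures ANOVA has 98% power with 22 completers, 97% with 20, 95% with 18 and 93% with 16. Attrition of the assumed size does not bring it below the stated 0.90.
- **A faulty sphericity rule.** In simulations with 22 patients and three visits, correcting only after a detected violation kept type I error close to 0.05 (at most about 0.055). The preliminary test had power 0.73 to 0.83 at epsilon 0.75 to 0.72. The rule needs no repair.
- **Bias always towards success.** Step 3 of the working shows that the direction depends on who is lost.
- **Loss of most of the sample in July 2026.** The timeline table presents that date as the end of all follow-up, not as an early data cut. Its conflict with nine months after April 2026 surgery is a separate matter of dates, and no model can supply 9-month values that were not collected.

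**Conclusion.** The point holds as a cheap improvement to the analysis. The named ANOVA discards observed ISQ and HU values whenever a visit is missing, in a study that itself anticipates withdrawal and implant failure. At assumed per-visit losses of 5 to 15%, about 7 to 20% of the recorded values would go unused.

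The effect on the estimate is probably small. It is roughly 3 to 6% too high if the two least stable of 22 implants are lost, about 4% too low if the two with the lowest baseline are lost, and nil for the 0-to-9-month change if loss follows the 3-month value. These sizes rest on the article's change of 4 (SD 1.86), normal data, and assumed loss patterns and baseline spread. The article states no failure or dropout rate.

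Separately, mean change should be declared as conditional on implant survival, whichever model is used.

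**What to change.** 1. Replace repeated measures ANOVA for ISQ and HU by a linear mixed model with time as a categorical factor, unstructured within-patient covariance, REML and Kenward-Roger degrees of freedom. Fit it to all observed values and keep the three Bonferroni-adjusted contrasts. State that missed visits are handled under missing at random. With an unstructured covariance no sphericity assumption is needed.
2. State that mean ISQ and HU change applies to surviving implants, and print the number of failures beside each estimate.
3. Add one sensitivity analysis that counts each failed implant as the worst outcome, for example a rank-based test of change with failures at the lowest rank. It gives a test, not a mean comparable with the main estimate, and should be presented that way.

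The cost is analysis wording and a few lines of code. No new data, visits or patients are needed. With complete data the estimated mean changes are unchanged, although standard errors may differ slightly because variances are no longer pooled across visits. The article reports that no outcome data are yet available; the change should be made and dated before any are analysed.
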